## **2. OBJECTIVE(S)**

### **2.1. Primary**

- To assess the levels of A $\beta$  isoforms and fragments in CSF after administration of GSK933776 in mild AD and MCI patients.

## **2.2. Secondary**

- To assess the relative amounts of A $\beta$  isoforms and fragments in CSF and plasma after administration of GSK933776 in mild AD and MCI patients as detected by IP-MALDI or similar technology.
- To assess the levels of A $\beta$  isoforms and fragments in plasma after administration of GSK933776 in mild AD and MCI patients
- To assess the levels of tau and phospho-tau in CSF after administration of GSK933776 in mild AD and MCI patients
- To assess the pharmacokinetics of GSK933776 in CSF and plasma in mild AD and MCI patients
- To assess PK/PD relationship of GSK933776 in CSF and plasma in mild AD and MCI patients
- To assess the safety and tolerability of GSK933776 in mild AD and MCI patients

## **3. ENDPOINT(S)**

### **3.1. Primary**

- The temporal changes of total A $\beta$  1-42 and free A $\beta$  1-42 levels in CSF after GSK933776 administration

### **3.2. Secondary**

- The temporal changes of total A $\beta$  1-42 and free A $\beta$  1-42 levels in plasma after GSK933776 administration
- The temporal changes of free A $\beta$  1-22+ and total A $\beta$  18-34 levels in plasma after GSK933776 administration
- The temporal changes of Tau and phosphor Tau – 181 levels in CSF and plasma after GSK933776 administration
- The temporal changes of A $\beta$  isoforms and fragments in CSF and plasma after GSK933776 administration as detected by IP-MALDI or similar technology
- Estimated pharmacokinetic parameters of AUC 10-22 h, Cmax and Tmax for GSK933776 in CSF and plasma
- Assessed PK/PD relationship by modelling
- The safety parameters of GSK933776:
  - Adverse event reporting and safety laboratory data
  - CNS Safety: MRI and MMSE
  - CVS safety: ECG and vital signs
  - Anti-GSK933776 antibodies

## 4. INVESTIGATIONAL PLAN

### 4.1. Study Design/Schematic

Figure 5 Study design

[figure not shown]

### 4.2. Discussion of Study Design

This is an open label, single dose study to assess short term pharmacodynamics of GSK933776 by intra-individual comparison and safety of GSK933776. Doses will be given as outlined in Figure 5 for option 1 and 2, where dose group 2 (0.1 mg/kg and 3 mg/kg) and dose group 3 (3mg/kg and 6mg/kg) are administered in parallel. The effect on the beta amyloid levels will be assessed in early (MCI) and mild AD patients after a single dose of GSK933776 by i.v. administration.

The first dose level used will be 1mg/kg, followed by either dosing option one: 0.1 and 3 mg/kg or dosing option two: 3 and 6mg/kg. The decision for option 1 or 2 will be based on the results from the 1mg/kg dose group. The patient may enroll into subsequent cohorts after the follow-up period.

CSF and blood samples will be continually collected at hourly intervals for 22 hours, which will include approximately up to 9 hours for baseline and 12 hours for post dose sampling. Based on the first 3 patients completed, the primary time period for statistical analysis is likely to be between 6-8 hours to assess the baseline level (with hours 0-5 considered as a run in period to get stable values). The time period between 2-5 hours post dose will likely be in the focus for the post-dose assessment for statistical analysis purposes. Full details of the assessments periods for baseline and post-dose will be defined in the Reporting Analysis Plan (RAP).

Following the completion of three mild AD subjects on the first dose level of 1mg/kg, the results of total and free A $\beta$  levels will be reviewed and the sample collection times for CSF and blood for both baseline and post dose may be adjusted according to the data observed from these subjects. The rationale for the data review after three subjects is the aim of reducing the total time of CSF sampling and the number of sampling time points to a minimum – in face of the limited data available for this methodology in Alzheimer's patients there is a need to initially take a conservative sampling approach.

If the data from these three subjects are insufficient due to variability or the time periods initially selected for baseline and post dose need to be adjusted, a further 3 subjects may be recruited to ensure evaluable data up to ten subjects to aid in the decision for the next dosing option. The safety, immunogenicity, biomarker, PK and PD samples will also be collected during the study following ongoing reviews of safety, tolerability and pharmacokinetics.

### 4.3. Treatment Assignment.

Subjects will be assigned to doses of GSK933776 in accordance with the randomization schedule produced using RandAll, a web-based clinical trials system, by QSci, Discovery Biometrics Biopharmaceuticals department at GSK, prior to the start of the study.

### 4.4. Investigational Product Dosage/Administration

|                                        |                                                                                                                                                                                                                                    |
|----------------------------------------|------------------------------------------------------------------------------------------------------------------------------------------------------------------------------------------------------------------------------------|
| Product name:                          | GSK933776                                                                                                                                                                                                                          |
| Formulation description:               | Antibody I.V. solution                                                                                                                                                                                                             |
| Dosage form:                           | i.v. injection                                                                                                                                                                                                                     |
| Unit dose strength(s)/Dosage level(s): | 50mg/mL, presented as 1 mL filled into in a 2 mL or 3 mL vial. The drug is supplied as a single use vial for intravenous administration and is not formulated with a preservative.                                   |
| Route/Administration/
Duration:     | Intravenous                                                                                                                                                                                                                        |
| Dosing instructions:                   | The dose will be administered through an i.v. catheter over approximately 1 hour                                                                                                                                                   |
| Device:                                | Vial                                                                                                                                                                                                                               |
| Method for individualizing dosage:     | GSK933776 will be diluted to the appropriate concentration in 0.9% Sodium Chloride (in infusion bags). The appropriate volume will be withdrawn into a syringe. Drug will then be administered using a Syringe Pump and a Catheter |

#### **4.5. Dose Escalation Decision/ Dose Adjustment/Stopping Criteria**

Safety parameters from this study and the first time in human study BA1106006 will be fully assessed before the next cohort is dosed. Any trends towards drug-related changes will be fully evaluated. The decision to dose escalate will be based on the nature, severity and frequency of any safety and/or tolerability observations. The decision will be made by a Study Review Team consisting of GSK's Clinical leader (CMTL), medical monitor and GCSP physician supported by the study manager, statisticians and the PK/PD modelling expert. The decision will be presented to the investigators.

The following parameters will be monitored carefully and will be reviewed by the GSK Medical Monitor, who may discuss the data with Investigator(s), prior to all dose escalations. If clinically significant findings as outlined below are observed in a significant number of subjects, then GSK933776 administration and dose escalation will be halted until all of the cumulative safety data is reviewed by the Study Review Team, the medical monitor and the GSK Global Safety Board.

##### **4.5.1. Pharmacokinetic Parameters**

Dose escalation will be terminated on pharmacokinetic grounds if the predicted mean AUC10-22h exceeds 686 mg.h/mL or Cmax exceeds 4.00 mg/mL. These values are based on preclinical toxicology studies and based on the experience from the first time in human study with GSK933776 are highly unlikely to be reached.

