### 1.1.5. Animal Toxicology of GSK933776

GSK933776 was well tolerated in the cynomolgus monkey following bi-weekly (one dose every 2 weeks) IV bolus administration for 6 weeks, at doses of 10, 50 and 100 mg/kg (the maximum dose tested). There was no evidence of any organ toxicity (including male and female reproductive organs) or immunogenicity. There was no evidence of delayed toxicity following an 8 week off-dose period in animals previously treated at 100mg/kg. The No Observed Adverse Effect Level (NOAEL) was 100 mg/kg. The mean systemic exposure (males and females combined) of GSK933776 at 100 mg/kg on Day 1 was 2.9 mg/mL (Cmax) and 384.5 mg.h/mL (AUC(0-14d)). The mean systemic exposure (male and females combined) on Day 29 was 4.00 mg/mL (Cmax) and 572 mg.h/mL (AUC(0-14d)). The mean plasma half life was determined as approximately 12.5 days. The NOAEL provides sufficient safety margins over the doses and predicted exposures in the proposed clinical study.

Following 39 weeks of dosing in the cynomolgus monkey (4/sex/group) at 0 (vehicle), 10, 50 and 100 mg/kg/dose once every two weeks (biweekly) by the intravenous route GSK933776, was well tolerated at all doses without evidence of toxicity (including delayed toxicity) or immunogenicity. The NOAEL for GSK933776 in cynomolgus monkeys was 100 mg/kg/dose [gender-averaged AUC(0-τ) 807 mg.h/mL, gender-averaged Cmax 5.09 mg/mL; based on Week 39 values]. Also there was no evidence of delayed toxicity or immunogenicity following an 8-week treatment-free period.

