#### 4.5.5.3. Blood coagulation and Platelets

- INR > 2
- Platelet count < 124,000/mm^3, or ≥ 40% change from baseline values

This protocol allows some alteration from the currently outlined dosing schedule, but the predicted maximum will not exceed 6mg/kg.

The decision to proceed to the next dose level of GSK933776, will be decided by the GSK Study Team and the investigator based on total and free amyloid steady levels in CSF and plasma, safety and tolerability data obtained at the prior dose level. The actual doses to be administered may be adjusted either an increase or a decrease in the planned doses.

The dosing schedule may also be adjusted to expand a dosing groups to further evaluate pharmacodynamic and safety findings at a given dose level, or to add dose group to evaluate up to 2 additional dose levels. The study procedures for these additional subject(s) or dose group(s) will be the same as that described for other study subjects.

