4. CSF and blood samples will be continuously collected every hour over a period of 22 hours, these include approximately 9 hours for baseline and 12 hours for post dose. After three and six subjects are completed, the results will be reviewed and the sample collection times for both baseline and post dose may be adjusted according to the data from these subjects.
5. This test is for the subject with women with childbearing potential only.
6. ECG and vital sign at 22 hour should be performed before patient leave the Clinical Unit
7. Follow-up day 7±1 day and follow-up day 56 ± 3 days

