**6.3.2.2. Pharmacokinetic Analyses**

Pharmacokinetic analysis will be the responsibility of the Clinical Pharmacokinetics Modeling and Simulation Department, QSci, GSK. Plasma (GSK933776) concentration-time data will be analyzed by non-compartmental methods according to GlaxoSmithKline guidance document, [REDACTED] with WinNonlin. Calculations will be based on the actual sampling times recorded during the study. From the plasma concentration-time data, the following pharmacokinetic parameters will be determined, as data permit: maximum observed plasma concentration (Cmax), time to Cmax (tmax), area under the plasma concentration-time curve post dose up to 22h [AUC (10-22h)].

Pharmacokinetic data will be presented in graphical and/or tabular form and will be summarized descriptively. All pharmacokinetic data will be stored in the Archives, GlaxoSmithKline Pharmaceuticals, R&D.

Statistical analyses of the pharmacokinetic parameter data will be the responsibility of Discovery Biometrics, GlaxoSmithKline.

Following loge-transformation, AUC & Cmax for GSK933776 in CSF and plasma may be separately analyzed using a mixed effects model. Point estimates and their associated 90% confidence intervals will be back-transformed to provide point estimates and 90% confidence intervals for the ratio (i.e. change from baseline) at each dose level. Further details of the model terms (random effects), possible covariates and interactions between treatment and covariates will be included in the RAP.

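### The PK stopping rule sets a multi-day-sized AUC limit (686 mg.h/mL) on a 12-hour AUC, so its AUC criterion can never act before its Cmax criterion

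*Protocol*

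**What the plan says.** Section 4.5.1 of the protocol terminates dose escalation on pharmacokinetic grounds "if the predicted mean AUC 10-22h exceeds 686 mg.h/mL or C max exceeds 4.00 mg/mL". It attributes both values to preclinical toxicology and says that neither is likely to be reached.

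Section 6.3.2.2 defines the AUC as "area under the plasma concentration-time curve post dose up to 22h [AUC (10-22h" h) and Cmax as "maximum observed plasma concentration (C max"). Section 4.2 describes the sampling as "approximately up to 9 hours for baseline and 12 hours for post dose sampling".

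Section 1.1.5 gives the monkey exposures at 100 mg/kg:

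- Day 1: Cmax 2.9 mg/mL and AUC(0-14d) 384.5 mg.h/mL.
- Day 29: the mean exposure "on Day 29 was 4.00 mg/mL (C max ) and 572 mg.h/mL (AUC(0-14d").
- Week 39: Cmax 5.09 mg/mL and AUC(0-τ) 807 mg.h/mL, with dosing every two weeks.

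Section 4.5.5.3 caps the dose: "the predicted maximum will not exceed 6mg/kg".

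**The concern.** The two criteria are joined by "or", so each should be able to stop escalation by itself: one guards against a high peak, the other against high total exposure. The second can do that only if its limit is on the scale of its interval. A value of 686 mg.h/mL is the size of the two-week monkey AUCs, yet it is applied to 12 hours. If the AUC criterion cannot be met unless the Cmax criterion has already been met by a wide margin, the rule has no working limit on total exposure, although a reader of Section 4.5.1 would believe that it has one.

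**Working it through.** **Inputs.** AUC limit 686 mg.h/mL and Cmax limit 4.00 mg/mL (Section 4.5.1); window 22 − 10 = 12 h (Sections 4.5.1 and 6.3.2.2, consistent with the 12 post-dose hours in Section 4.2); monkey exposures and the 12.5-day half-life (Section 1.1.5); product strength 50 mg/mL (Sections 4.4 and 11); top dose 6 mg/kg (Section 4.5.5.3).

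**Source of the limits.** The Cmax limit of 4.00 mg/mL equals the Day 29 monkey Cmax. The AUC limit of 686 equals none of the reported AUCs (384.5, 572, 807), so its derivation cannot be reproduced from the protocol. Appendix 7 (Amendment 1, Change 08) shows that the same number was once attached to AUC(0-inf). That explains the mismatch; the fault lies in the current text.

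**The bound.** For any concentration curve, AUC over a window ≤ Cmax × window length. This also holds for the linear trapezoidal rule and for means over subjects.

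- Largest AUC(10-22h) with Cmax at its limit: 4.00 × 12 = 48 mg.h/mL.
- As a share of the AUC limit: 48 / 686 = 7.0%.
- Average concentration needed to reach the limit: 686 / 12 = 57.2 mg/mL, which is 57.2 / 4.00 = 14.3 times the Cmax limit and above the 50 mg/mL of the undiluted product.
- Time at a constant 4.00 mg/mL to accumulate 686: 686 / 4.00 = 171.5 h, or 7.1 days.

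**Other readings.**

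- *Longer window.* The Time and Events Table allows dosing after a last baseline sample at 7 to 11 h. Counting from 7 h gives 15 h and a ceiling of 15 × 4.00 = 60 mg.h/mL.
- *Cmax as a mean or as an individual value.* The bound holds for both.
- *AUC predicted for the next dose, Cmax observed at the current dose.* The first cohort always receives 1 mg/kg, so the largest step is six-fold, to 6 mg/kg. Assuming dose proportionality, the ceiling is 6 × 48 = 288 mg.h/mL, still below 686. Passing 686 would need exposure to rise more than 14.3-fold for a six-fold dose.

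**Expected exposure at 6 mg/kg.** This assumes linear scaling from monkey Day 1 at 100 mg/kg, a factor of 0.06.

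| Quantity | Calculation | Result | Share of stated limit |
|---|---|---|---|
| Cmax | 2.9 × 0.06 | 0.174 mg/mL | 4.4% of 4.00 |
| 12-hour AUC, at most | 0.174 × 12 | 2.09 mg.h/mL | 0.3% of 686 |
| AUC(0-14d) | 384.5 × 0.06 | 23.1 mg.h/mL | 3.4% of 686 |
| AUC(0-inf) | 23.07 / 0.540 | 42.7 mg.h/mL | 6.2% of 686 |

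The 0.540 is the fraction of AUC(0-inf) within 14 days under mono-exponential decline: 1 − 2^(−14/12.5). If human exposure were 0.5 to 3 times the scaled value (an assumed range), AUC(0-inf) would be about 21 to 128 mg.h/mL, or 3% to 19% of 686.

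**The case against.** The best defence is that nothing turns on this. Section 4.5.1 presents the limits as a remote backstop. The dose cannot exceed 6 mg/kg, and that dose was well tolerated when given three times in the first-in-human study. Section 1.2.4 requires eight weeks of first-in-human safety data at a dose level before 3 or 6 mg/kg is given, and Section 4.5 adds a Study Review Team decision. The 3 and 6 mg/kg groups now run in parallel, so there is essentially one escalation decision. All of this stands, and it limits the consequence. It does not repair the rule: a limit that is unlikely to be reached differs from one that cannot act within its own rule.

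Two narrower objections also have some force. The bound is pure arithmetic only if AUC and Cmax refer to the same dose; the mixed reading needs an assumption about dose proportionality, though the conclusion survives with a wide margin. And because the source of 686 is not shown, the absence of a 12-hour basis in the protocol does not prove that none exists. The redundancy does not depend on that source.

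**Conclusion.** The rule is wrong as written. With both criteria read at the same dose, the AUC criterion cannot be met without Cmax exceeding its limit at least 14.3-fold. This needs no assumption beyond the 12-hour window. On the mixed reading it remains out of reach under dose proportionality (288 against 686). Only the Cmax criterion can stop escalation.

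The consequence is modest. Under the scaling assumption, a correctly matched AUC limit would very probably not be reached either, so this is a mismatched safety criterion and not a likely missed stop. It still merits correction, because the protocol states a limit on total exposure that it does not in fact impose.

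**What to change.** In Section 4.5.1, put the limit and the interval on the same basis and state where the limit comes from. The simpler course is to apply 686 mg.h/mL to a predicted AUC over the interval of its toxicology basis, such as AUC(0-14d) or AUC(0-inf). The alternative is to keep AUC(10-22h) and restate the limit from toxicology data on a 12-hour basis. Merely choosing a value under 48 would not do, since a limit just below that ceiling would still be almost redundant. For scale only, 686 spread evenly over 14 days is 686 × 12 / 336 = 24.5 mg.h/mL per 12 hours. The sponsor's safety and PK team should choose.

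The cost is one amended sentence and, for the long-interval option, a short statement of how the AUC is predicted, because Section 6.3.2.2 plans only the non-compartmental AUC to 22 h. Modelling would be needed, since the only visits scheduled after the in-house phase are "Follow-up day 7±1 day and follow-up day 56 ± 3 days". The rule already uses a predicted mean, and Section 4.5 already gives the Study Review Team a PK/PD modelling expert. The 12-hour option uses the sampling already planned.

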##### **4.5.2. Adverse Events**

Dose escalation to subsequent cohorts may be stopped if one or more subjects experience dose limiting drug related adverse events or if the pattern of adverse events observed in a cohort is consistent across subjects, poorly tolerable and clinically significant.

Individual subjects may be withdrawn if they show poor tolerability with respect to signs and symptoms, or if there is evidence of clinically important changes in safety assessment results (including vital signs, weight, clinical laboratory tests, ECGs, MRIs, and physical and neurological exams).

##### **4.5.3. Cognitive and Neuropsychological Assessment**

A subject's Mini Mental State Examination (MMSE) score will be assessed at screening as part of the study inclusion criteria, 56 days post dosing. MMSE will be used to detect any unexpected clinically significant deterioration in cognition. If at any visit, deterioration is suspected, MMSE will then also be performed to help quantify the degree of deterioration. In this case brain MRI scans and EEGs will also be obtained from the same subjects. MMSE will then be repeated 3-weeks later to assess whether the change was maintained. Both the brain MRI scan and EEG will also be repeated at these time points. Subjects with any abnormality at the brain MRI scan and/or EEG will be followed up to assess reversibility of these findings.

If at any point 50% or more subjects in a cohort experience unexplained cognitive deterioration that in the opinion of the Investigator is not compatible with the subjects' expected natural history of AD, dosing will be suspended for subsequent cohorts. The Study Review Team (see Section 4.5) will review these data together with all other available safety information to decide if it is necessary to stop the study.

#### 4.5.4. Liver Function Criteria

Liver chemistry threshold stopping criteria have been designed to assure subject safety. When subjects meet the following liver chemistry threshold criteria, the subject will be not entered in the second cohort and must be permanently withdrawn from the study, and the subject monitored until liver chemistries resolve, stabilize, or return to baseline values. The subject must be permanently withdrawn from the study if he/she meets following criteria:

- ALT  $\geq$  3xULN **and** bilirubin  $\geq$  1.5xULN (>35% direct).
- ALT  $\geq$  3xULN.

Subjects with ALT  $\geq$  3xULN **and** bilirubin  $\geq$  1.5xULN (>35% direct bilirubin; bilirubin fractionation required) must be required to return to the clinic (within 24 hours) for repeat liver chemistries and additional testing, and monitored closely (with specialist or hepatology consultation recommended). This event must be reported to GSK within 24 hours of learning of its occurrence. Subjects must be monitored twice weekly until liver chemistries (ALT, AST, alkaline phosphatase, bilirubin) resolve, stabilize or return to within baseline values.

Subjects with ALT  $\geq$  3xULN must be monitored weekly until liver chemistries (ALT, AST, alkaline phosphatase, bilirubin) resolve, stabilize or return to within baseline values. This event must be reported to GSK within 24 hours of learning of its occurrence.

In all the above situations, every attempt must be made to obtain the following:

- Viral hepatitis serology including:
  - Hepatitis A IgM antibody.
  - Hepatitis B surface antigen and Hepatitis B Core Antibody (IgM).
  - Hepatitis C RNA.
  - Cytomegalovirus IgM antibody.
  - Epstein-Barr viral capsid antigen IgM antibody (or if unavailable, obtain heterophile antibody or monospot testing).
  - Hepatitis E IgM antibody (if subject resides outside the USA or Canada, or has travelled outside USA or Canada in past 3 months).
- Blood sample for pharmacokinetic (PK) analysis, obtained within 56 days of last dose. Record the date/time of the PK blood sample draw and the date/time of the last dose of investigational product prior to blood sample draw on the CRF.

- Serum creatinine phosphokinase (CPK) and lactate dehydrogenase (LDH).
- Fractionate bilirubin, if bilirubin  $\geq 1.5 \times \text{ULN}$ .
- Record the appearance or worsening of clinical symptoms of hepatitis, or hypersensitivity, fatigue, decreased appetite, nausea, vomiting, abdominal pain, jaundice, fever, or rash as relevant on the AE report form.
- Record use of concomitant medications, acetaminophen, herbal remedies, other over the counter medications, putative hepatotoxins, or alcohol on the concomitant medications report form.
- The following are required for subjects with ALT  $\geq 3 \times \text{ULN}$  **and** bilirubin  $\geq 1.5 \times \text{ULN}$  but are optional for other abnormal liver chemistries:
- Anti-nuclear antibody, anti-smooth muscle antibody, and Type 1 anti-liver kidney microsomal antibodies.
- Liver imaging (ultrasound, magnetic resonance, or computerized tomography) to evaluate liver disease.

